### Process evaluation

A process evaluation will be carried out as described by previous research [18].

The following outcomes assessed: The proportion of the population of the intended target population that actually participated in the intervention, the number of patients who completed the intervention, the mean number of CBT sessions and patient satisfaction of the intervention and patient information leaflets.

### Sample size

Complete outcome data is expected to be available on 112 patients per group (224 in total). This gives 80% power to detect a standardised difference of 0.375 (equivalent to a change in HADS-A of at least 1.5 when standard deviation is assumed at 4) assuming a type 1 error rate of 5%.

### Analysis

An “Intention to treat” analysis is planned. Descriptive statistics will be used for analysis. The sample size calculation assumes that groups will be compared using an independent *t*-test (the primary outcome variable being the HADS-A score at three months). For data collected at multiple points in time, a longitudinal analysis will be undertaken. This will involve comparing the way HAD scores change over time in the different trial arms using repeated measures analysis of variance such as a mixed effects or multilevel model (repeat assessments nested within patients). This will make use of all the observed data for a patient even if they missed one or more time points. Finally the effect of missing data on our results will be estimated.

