### Randomisation

Patients enrolled in the study are randomised on a 1:1: basis to CBT or control using a computer generated software package after signing the consent form. Patients are stratified at randomisation for COPD disease severity using NICE 2010 categories (mild to moderate and severe to very severe) and age. Patient initials, date of birth and severity of COPD are entered into the web-based system, which returns the allocation status. Patients are informed of their treatment group following randomisation.

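### The only method tied to 3-month HADS-A is an unadjusted t-test, and no primary analysis is named; a baseline-adjusted one would gain precision at no cost

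*Protocol article*

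**What the plan says.** Three parts of the protocol article bear on this.

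- **Analysis.** The sentence on the primary outcome sets out what the sample size calculation presupposes, namely that "groups will be compared using an independent *t*-test (the primary outcome variable being the HADS-A score at three months"). The next sentences plan a longitudinal comparison of HAD scores between arms, by repeated measures analysis of variance such as a mixed or multilevel model, which keeps patients who missed a visit. Neither method is called the primary analysis, and no covariates are given for either.
- **Sample size.** On numbers, the section states: "Complete outcome data is expected to be available on 112 patients per group (224 in total"). On power, it states: "This gives 80% power to detect a standardised difference of 0.375", which the article describes as "equivalent to a change in HADS-A of at least 1.5 when standard deviation is assumed at 4". The type 1 error rate is 5%.
- **Randomisation.** "Patients are stratified at randomisation for COPD disease severity using NICE 2010 categories (mild to moderate and severe to very severe) and age". Date of birth and COPD severity are entered into the system that returns the allocation.

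Baseline HADS-A is also held for everyone. Table 1 lists it at baseline and at all three follow-ups, and a score of at least 8 is an inclusion criterion.

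**The concern.** A two-sample t-test on the 3-month score uses the outcome and the arm, and nothing else. If it became the primary analysis, three things would follow.

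1. The part of the 3-month score that baseline HADS-A predicts would stay in the residual variance, and any chance imbalance in baseline anxiety would stay in the estimate.
2. The trial balances on COPD severity and age. When such factors are prognostic, an unadjusted test after stratified randomisation tends to give a standard error that is too large.
3. Patients without a 3-month score would contribute nothing to that test.

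The article also offers two candidate analyses for HADS-A without ranking them, so as written the choice between them could be made after the data are seen.

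What is at stake is efficiency and pre-specification. The design meets its 80% target with no margin, so precision that costs nothing is worth having.

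**Working it through.** **Inputs from the article.** Difference 1.5 points, SD 4 (standardised 1.5/4 = 0.375), 112 per arm with outcome data, 1:1 allocation, 5% type 1 error, 80% power. Sidedness is not stated.

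**Step 1: reproduce the plan's figure.**

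n per arm = 2 × (1.960 + 0.842)² / 0.375² = 2 × 7.85 / 0.1406 ≈ 111.6, rounded up to 112. This matches.

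Power at 112 per arm: SE = 4 × √(2/112) = 0.535; 1.5/0.535 = 2.806; 2.806 − 1.960 = 0.846; Φ(0.846) = 0.801. The exact noncentral t gives 0.798. A one-sided test would need only 88 per arm, so the planned calculation is two-sided and unadjusted.

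**Step 2: adjust for baseline HADS-A.** With r the correlation between baseline and 3-month HADS-A, a linear model with baseline as covariate has residual SD = 4 × √(1 − r²). The residual variance therefore falls by the fraction r². The article gives no r, so r is an assumption, shown here from 0.3 to 0.6. The entry rule of HADS-A ≥8 cuts off the lower part of the baseline range and may reduce r, which is why the lower end deserves weight.

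Worked case, r = 0.5: SD = 4 × √0.75 = 3.464; SE = 3.464 × √(2/112) = 0.463; 1.5/0.463 = 3.24; 3.24 − 1.96 = 1.28; Φ(1.28) = 0.90.

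| r | Residual SD | Variance reduction | Power, normal | Power, t-based | Detectable difference at 80% power | 95% CI half-width | n per arm for 80% power |
|---|---|---|---|---|---|---|---|
| unadjusted | 4.000 | 0 | 0.801 | 0.798 | 1.50 | 1.05 | 112 |
| 0.3 | 3.816 | 9% | 0.837 | 0.834 | 1.43 | 1.00 | 102 |
| 0.4 | 3.666 | 16% | 0.865 | 0.862 | 1.37 | 0.96 | 94 |
| 0.5 | 3.464 | 25% | 0.900 | 0.897 | 1.30 | 0.91 | 84 |
| 0.6 | 3.200 | 36% | 0.939 | 0.937 | 1.20 | 0.84 | 72 |

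Detectable difference = (1.960 + 0.842) × SE; half-width = 1.96 × SE; n uses the Step 1 formula with the residual SD. The two power columns differ by at most 0.3 percentage points.

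**Step 3: stratification factors.** The article does not say how strongly severity or age predicts HADS-A, so any further gain from adjusting for them cannot be computed.

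**Step 4: how baseline enters matters.** Using baseline in some form is not enough. If the contrast is the difference in change from baseline, and the SD is taken as 4 at both times (an assumption), the SD of the change is 4 × √(2(1 − r)). The n per arm for 80% power is then 157, 134, 112 and 90 for r = 0.3, 0.4, 0.5 and 0.6. Under that assumption a change-score contrast needs more patients than the t-test when r is below 0.5, and more than covariate adjustment throughout this range.

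**The case against.** The strongest case against the point is that nothing here is wrong. The sentence on the t-test opens by saying what the sample size calculation assumes, so it records a planning assumption. The same section plans a mixed model that uses all observed HAD scores, and it promises to estimate the effect of missing data. Table 1 puts HADS-A at baseline among the repeated measurements, so that model may well use it. Covariate lists commonly sit in a full protocol or SAP, and neither is shown.

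Much of this stands, and it rules out three stronger readings that a reader might infer:

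- *That the t-test is the declared primary analysis.* The article does not say so.
- *That the plan as a whole ignores baseline HADS-A and discards patients without a 3-month score.* Both statements are true of the t-test only. The mixed model is expressly meant to keep patients with missed visits.
- *That the trial is biased or underpowered.* The unadjusted test is valid under randomisation, and the stated sample size is correct.

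Nor does the article support calling baseline HADS-A the strongest predictor of outcome. At r = 0.3 the gain is modest, from about 80% to 83% power.

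What the objection does not remove is that the article goes beyond leaving covariates unstated. It attaches one specific, unadjusted test to the primary outcome, adds a second model with no stated 3-month contrast, and does not rank them. That is a stated choice, and it can be improved.

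**Conclusion.** The point holds as a worthwhile improvement in efficiency and clarity; it does not identify an error. The only method linked to 3-month HADS-A is unadjusted, and the article does not say whether it or the mixed model is primary. If the t-test were used as the primary analysis, the trial would give up precision that its own baseline data could supply. With 112 per arm and a 1.5-point difference, adjustment for baseline would move power from about 80% to 83-94%, and the detectable difference from 1.50 to 1.43-1.20 points.

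These figures rest on an assumed r of 0.3-0.6, on the article's SD of 4 applying to the 3-month score, and on a linear relation between baseline and outcome. The direction of the gain does not depend on the exact r, but its size does. Any added gain from severity and age is unquantified.

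**What to change.** Name one primary analysis in the Analysis section. Either of these would serve:

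- a linear model of 3-month HADS-A on arm; or
- the 3-month arm contrast from the mixed model already planned.

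Whichever is chosen, adjust for baseline HADS-A as a continuous covariate, COPD severity stratum and age. If the mixed model is chosen, state that baseline enters as a covariate and not through a change-from-baseline contrast. Keep the t-test as the sample-size basis, where it is conservative, and as a supportive analysis.

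The cost is a sentence or two of wording, fixed before the outcome data are examined. It needs no new data, no extra patients and no change to the sample size.

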### Primary outcome

The primary objective is to investigate if CBT delivered by respiratory nurses with either advanced CBT training (Post Graduate Diploma) or basic training in CBT techniques, reduces anxiety. The HADS Hospital Anxiety & Depression Scale (HADS) will be used to measure anxiety. Patients will be followed up at three, six and twelve months following randomisation into the study. The effects of the CBT intervention will be compared to usual care. A standardised manualised brief CBT intervention will be used. 224 patients will be required to complete the primary outcome at three months (112 in each arm). Patients will be stratified according to severity of COPD and age at randomisation.

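### The plan does not say which analysis gives the primary 3-month HADS-A result, and the only method linked to it by name, a t-test, drops randomised patients without that score

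*Protocol article*

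**What the plan says.** The Analysis section of the protocol article opens with the population label: "An “Intention to treat” analysis is planned". It does not define the label further.

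The next relevant sentence begins "The sample size calculation assumes that groups will be compared using an independent" t-test and identifies the endpoint in a parenthesis: "the primary outcome variable being the HADS-A score at three months". This is the only place in the section where a method and the primary outcome appear together.

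The section then plans a longitudinal analysis for data collected at several time points: a repeated-measures analysis such as a mixed effects or multilevel model, comparing how HAD scores change over time between arms. Of this model it says: "This will make use of all the observed data for a patient even if they missed one or more time points". It closes by promising that the effect of missing data will be estimated, without naming a method.

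The sample size counts patients with the outcome. Under Primary outcome: "224 patients will be required to complete the primary outcome at three months". Under Sample size: "Complete outcome data is expected to be available on 112 patients per group (224 in total").

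The trial is open, and the Randomisation section states: "Patients are informed of their treatment group following randomisation". Table 1 shows HADS-A collected at baseline, at 12–14 weeks, and at 6 and 12 months.

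**The concern.** Two analyses could produce the 3-month result, and they treat incomplete patients differently. The t-test uses only patients with a 3-month HADS-A and makes no use of the baseline score. The mixed model can use every patient's observed scores. The text links the first to the primary outcome, describes the second as a comparison of change over time, and names neither as primary. Either could be reported as the primary intention-to-treat result without departing from the text, and in an open trial that choice should be fixed before the data are seen.

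The choice matters if loss before the 12–14 week visit differs by arm and is related to anxiety. Patients know their allocation. CBT patients are offered two to six nurse sessions, while controls receive leaflets and advice to contact primary care, so reasons for not returning could differ. If more anxious CBT patients stop attending, the completers' comparison flatters CBT. If more anxious controls stop attending, it works against CBT.

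**Working it through.** **1. The plan's own figure.** Inputs from Sample size: difference 1.5, SD 4 (standardised difference 0.375), power 80%, type I error 5%, taken as two-sided.

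n per arm = 2 × (1.96 + 0.8416)² / 0.375² = 111.6, so 112. Power at 112 per arm is 0.801 by the normal approximation and 0.798 by the noncentral t. The stated 112 per arm reproduces. It is a number of patients with the outcome, not a number randomised.

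**2. Bias of a completers' difference.** Let d be the proportion missing in an arm and D the number of points by which missing patients score worse than completers, taken as the same in both arms. The full-arm mean is the completers' mean + d × D, so

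overstated CBT benefit = (d_CBT − d_control) × D.

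The documents give neither d nor D, so all values are assumptions:

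| Missing, control vs CBT | D (points) | Overstated benefit | Share of 1.5 |
|---|---|---|---|
| 10% vs 10% | any | 0 | 0% |
| 10% vs 20% | 1.5 to 4 | 0.15 to 0.40 | 10% to 27% |
| 10% vs 30% | 1.5 to 4 | 0.30 to 0.80 | 20% to 53% |

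**3. Loss weighted to high baseline scores.** Assume no true effect, SD 4 at both visits, baseline to 3-month correlation 0.4 to 0.6, 20% CBT loss weighted to patients above the median baseline, and 10% control loss unrelated to score. For a normal baseline the means of the upper and lower halves differ by 2 × √(2/π) × 4 = 6.38 points.

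- CBT loss 10% below and 30% above the median: the upper half makes up 0.35 / 0.80 = 0.4375 of completers. The baseline mean shifts by (0.4375 − 0.5) × 6.38 = −0.40, and the 3-month mean by −0.40 × (0.4 to 0.6) = −0.16 to −0.24.
- CBT loss 0% below and 40% above: the upper half makes up 0.30 / 0.80 = 0.375. The baseline mean shifts by −0.125 × 6.38 = −0.80, and the 3-month mean by −0.32 to −0.48.

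Simulations of the same scenarios under several assumed baseline distributions gave a false benefit of 0.15 to 0.50 points. Conditioning on baseline gave −0.03 to 0.02. Exchanging the arms in these assumptions gives the same sizes against CBT.

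**4. Effect on the error rate.** SE = 4 × √(2/112) = 0.535. The two-sided rejection rate with no true effect and bias b is 1 − Φ(1.96 − b/SE) + Φ(−1.96 − b/SE):

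- b = 0.15: 5.9%
- b = 0.20: 6.6%
- b = 0.40: 11.6%
- b = 0.50: about 15.4%

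**5. What the model repairs.** Simulation with no true effect, 140 per arm, 2,000 runs, correlation 0.5, about 20% missing in control (unrelated to score) and 24% in CBT:

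| CBT dropout depends on | Completers' difference | Estimate using baseline |
|---|---|---|
| Baseline HADS-A (observed) | −0.40 | 0.00 |
| 3-month HADS-A (unseen when missing) | −0.82 | −0.63 |

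The baseline-using estimate removes the bias in the first case and only part of it in the second.

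**The case against.** A reader might infer that the primary analysis is fixed as a completers' t-test and that missing-data protection is confined to a secondary analysis. The text supports neither. The t-test is worded as what the sample size assumes, and sizing on a t-test while analysing with a longitudinal model is common. The model is never called secondary. HADS-A at 3 months is one of its time points, and it is expressly said to use partial data. Stating how many completers are needed is a normal way to size a trial and does not exclude anyone from analysis. The closing promise on missing data is not limited to secondary outcomes, and its method may sit in an analysis plan that is not shown, so lack of that detail is no fault here.

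A reader might also infer that any loss related to anxiety biases the t-test, or that bias towards CBT has been shown. Loss that acts the same way in both arms gives zero bias when there is no true effect, and unequal loss unrelated to score also gives none. No dropout figure is stated, the upper end of the range needs a steep pattern confined to the CBT arm, and the opposite pattern would work against CBT. Both arms share the same follow-up schedule and routine clinic care, which limits how far attendance need differ.

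All of this stands. It narrows the point but does not remove it: no sentence says which analysis is primary, and the one method placed beside the primary outcome is the one that drops patients.

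**Conclusion.** The point holds as an unresolved choice of primary analysis with a real bias risk attached. The text permits a completers' comparison to be reported as the intention-to-treat result, although a better method is already planned.

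The size is conditional. With 20% CBT and 10% control loss, and CBT loss weighted to high baseline scores, the false benefit is roughly 0.15 to 0.5 points, or 10% to 33% of the 1.5-point target, and the type I error about 6% to 15%. These rates are assumptions. With loss that acts equally in both arms the bias is zero, and under other patterns the sign reverses. The change is worth making because it costs little and does not depend on which pattern occurs.

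**What to change.** In the Analysis section, name as primary the arm difference in HADS-A at 3 months from the mixed model already planned. Fit it to all randomised patients as allocated, with baseline HADS-A included so that patients without a 3-month score still contribute. Keep the t-test on observed 3-month scores as a supporting analysis only.

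The model relies on data being missing at random. The already promised estimate of the effect of missing data should therefore cover dropout that depends on the unseen 3-month score, for example by shifting the missing scores over a range of values separately by arm.

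The cost is a few sentences, slightly more analysis work and reliance on that modelling assumption. No extra patients or data are needed, since HADS-A is already collected at all four visits.

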### Health economic evaluation

An economic evaluation will be undertaken. Costs of respiratory admissions, cost of CBT intervention, cost of attending clinic, QALY’s (Quality of adjusted life year saved as per EQ5D) will be assessed.

### Trial steering committee

A trial steering committee has been formed to advise and monitor the study. The steering committee includes a patient and carer with COPD and a representative from the British Lung Foundation Charity. The committee has a number of experts and patient representatives including:

• Consultant Chest Physician (Chair).

• Representative for the British Lung Foundation and advisor for service users.

• A carer & service user.

• An expert in trial design.

• Respiratory Nurse Consultant & CBT therapist (Trial management/.Recruitment/Consent/Cognitive Behavioural Therapy & training respiratory nurses).

• A Chest Physician & academic researcher.

• Head of Nursing and Midwifery Research, an expert in research ethics and governance.

• A Clinical Psychologist will advise the project team particularly in respect of development of manualised training and provide clinical supervision.

• Medical statistician.

There will be overall oversight by a Trials Steering Committee (TSC) that will meet three times a year. As CBT is frequently undertaken within clinical care it is envisaged that this study poses minimum safety risks therefore a decision has been made not to have a separate study management group. However, recruitment, quality of data and safety of participants will be reviewed at each trial steering committee.

## Discussion

This study design has evolved through literature review, contact with published authors, a case series defining local COPD anxiety & depression rates [19] and a non-randomised case series of CBT in COPD [17]. Further study design refinement was through the National Institute of Health Research Design Service. This research builds upon and extends the prior work [15,16,20-24]. The study will address impact, feasibility and efficacy of teaching CBT skills to non-mental health professionals (such as respiratory nurses), to treat anxiety and depression in a clinical population of COPD patients. This is particularly important as there is a national shortage of CBT therapists. In routine clinical practice, CBT delivery by respiratory nurses could be the most realistic and potentially cost effective model to provide psychological care for patients with COPD. Respiratory nurses are front line staff who work with high volumes of COPD patients and will have the skill sets that may allow distinction between organic and psychological causes of breathlessness. The ability to integrate aspects of COPD care within one (familiar) setting such as a respiratory clinic or with familiar staff may help reduce barriers to engagement with the mental health aspects of COPD.

## Abbreviations

BMI: Body mass index; CAT: COPD assessment test; CBT: Cognitive behavioural therapy; CLRN: Clinical research network; COPD: Chronic obstructive pulmonary disease; EQ5D: Euroqol- 5 health state; FVC: Forced vital capacity; FEV1: Forced expiratory volume; QALY’s: Quality of adjusted life year saved; HADS: Hospital anxiety & depression scale; MRC: Medical research council; NHS: National health service; NIHR: National Institute of Health Research; TSC: Trial steering committee.
